#### Randomisation

Randomisation of participants to either the INT or CAU group will be done using a random allocation sequence, generated by a researcher not involved in the project, using a computer-based random number generator. A pre-prepared series of sealed opaque envelopes, each labelled with a participant ID number and containing a Randomisation Notification Letter, will be used to conceal the group allocation from researchers and participants until after completion of the baseline assessment. Participants in either group will continue to access their regular medical treatment with their child’s diabetes team.

Immediately after completion of the baseline home observation session, the research assistant conducting the home visit will open the envelope, and participants will be notified of their condition. The Randomisation Notification Letter will be provided to the participant to retain for their records.

Participants will be assigned to intervention sessions based on individual preferences for day, time, and location, depending on availability of groups. Participants will be assigned to intervention sessions as soon as possible after randomisation. The flow of participants through the study is summarised in Fig. 1.

**Fig. 1 Fig1:**
[figure not shown]
Participant flow through the study

Due to the nature of the intervention, neither participants nor research staff can be blinded to condition allocation, with the exception of coders who will code randomly-allocated video files of home observation sessions and remain blinded to participant allocation and assessment time-point. Since other research staff will not be blinded to allocation, a data monitoring committee is not needed.

### Intervention

The intervention will consist of two, 2-h *Positive Parenting for Healthy Living* group discussion sessions. The content of the sessions draws on the theoretical principles that form the basis of Triple P [32]. The sessions are designed to be interactive and provide opportunities for discussion.

The proximal targets of the intervention are parenting skills and confidence relating to both general child behaviour, and behaviour problems specific to illness management. The intervention aims to increase parental self-regulation, promote child self-regulation, increase positive parenting practices to promote child cooperation (particularly relating to illness management), lead to consistent discipline and promote routine, and enhance parents’ capacity to take care of themselves in order to reduce parenting stress and improve family wellbeing. The intervention will be conducted by parents with their children and there will be no direct contact with children in terms of intervention delivery.

#### Positive parenting for healthy living – part I

The first session is designed as an introduction to the principles of positive parenting in the context of child chronic illness management. It begins by exploring the impact of the child’s condition on the child, parent, and family, and introduces the principles of positive parenting as a way to promote children’s development and manage children’s behaviour and emotions in a constructive way.

It aims to assist parents to develop strategies to manage their child’s condition effectively while minimising the impact on the child and family by continuing regular activities, having realistic expectations of their child and themselves, involving the child in age-appropriate diabetes management tasks, reducing child and family stress, balancing work and family, working as a team, communicating effectively with the child’s diabetes team and caregivers, and helping siblings cope.

#### Positive parenting for healthy living – part II

The second session will be conducted one week after the first session. It aims to build on the principles of positive parenting introduced in Part I, to promote positive practices, assist parents to develop effective disciplinary methods, and help create environments conducive to caring relationships between parents and their children. It begins with a discussion of why children with chronic health conditions may be at risk of behaviour problems, before examining common parenting traps from the perspective of parenting a child with a chronic illness. The session focuses on providing parents with strategies that will empower them to prevent and manage problem behaviours and ensure their children are implementing their illness prevention and management plan appropriately (e.g., taking medication as prescribed, using devices correctly). Assertive discipline strategies are also discussed, including giving clear instructions, using praise effectively, and managing disobedience and problem behaviour.

Parents will also be provided with a ‘Communicating with Others’ tip sheet, developed for this study, outlining suggestions for how to effectively communicate and work together with the child’s other caregivers and health care professionals*.* Finally, parents will be encouraged to take their child to regular, ongoing visits with their diabetes team.

##### Care as usual condition

Families in CAU will complete assessments at baseline, 6 weeks later, and then again at 6 months. During this time, families will continue to receive regular medical management from their usual diabetes team, as appropriate. After the 6-month follow-up assessment, families will be offered participation in the intervention.

##### Protocol adherence

Each practitioner delivering the intervention will be trained using a standardised system of training and accreditation, designed to promote program use and fidelity. Practitioners deliver Triple P according to a standardised manual and follow treatment delivery protocols, and complete protocol adherence checklists for each session conducted. These will be reviewed and coded by a research assistant familiar with the protocols for adherence. Practitioners will receive regular clinical supervision. Group sessions will be videotaped and independently coded for protocol adherence, using structured session checklists. The inter-rater reliability (kappa) of this coding will be assessed for 25 % of videotaped sessions by a second rater.

#### Child behaviour and adjustment

##### Parent-report

General child behaviour will be assessed using the *Child Adjustment and Parent Efficacy Scale* (CAPES) [52], a 30-item measure of parental perceptions of child behavioural and emotional adjustment. Parents rate each item from 0 (*Not true at all*) to 3 (*True most of the time*) depending on how true the statement was for their child in the past 4 weeks. Items are summed to yield a total intensity score (range of 0–90), a behaviour score (range of 0–78), and an emotional maladjustment score (range of 0–12), where higher scores indicate higher levels of problems. The Confidence Scale consists of 20 items and measures parents’ level of confidence in managing child emotional and behavioural problems. Parents rate each item from 1 (*Certain I can’t do it*) to 10 (*Certain I can do it*) depending on how confident they are in successfully dealing with their child’s behaviour. The possible range for this scale is 20–200, with higher scores indicating greater levels of parent efficacy. This measure has demonstrated good internal consistency for both Intensity (*α* = .90 and .74 for behavioural and emotional subscales, respectively) and Confidence (*α* = .96) scales [53].

#### Child’s quality of life

##### Parent-report

Children’s health-related quality of life will be assessed using the *PedsQL4.0: Pediatric Quality Generic Core Scale* [54], which is a 23-item measure assessing the core dimensions of health (physical, emotional, social and school functioning). Parents rate each item from 0 (*Never*) to 4 (*Almost always*) depending on how true the statement was for their child in the past month. Two summary scores (physical and psychosocial health) and a total score are calculated. Items are reverse-scored and transformed on a scale from 0-100 (0 = 100, 1 = 75, 2 = 50, 3 = 25, 4 = 0), and mean item scores are used to calculate summary and total scores. Higher scores indicate better quality of life. It has high internal consistency (α = .90), distinguishes between healthy children and children with acute and chronic health conditions, as well as disease severity within a chronic health condition, and is sensitive to change.

### Secondary outcome measures

#### Child’s illness severity and control

##### Parent-report

Parents will provide diabetes-specific information as well as information regarding the child’s illness severity and control at baseline, including the child’s age at diagnosis, the date and value of child’s most recent HbA1c, target blood glucose ranges (before meals, after meals, at bedtime and overnight), the current treatment regime (insulin/pump therapy/use of continuous blood glucose monitoring device), parent-child responsibility-sharing in diabetes management, and frequency and description of hospitalisations due to diabetes complications.

##### Monitoring

To obtain an indication of short-term metabolic control, parents will also be asked to provide a record of routine blood glucose readings (from the child’s blood glucose meter or a paper diary) for the last 28 days. The readings will be directly downloaded from the child’s blood glucose meter at each home visit session (via Diasend software: www.diasend.com/au/), and a copy of readings will be taken for those keeping a diary record. After the readings are downloaded, the researcher will ask the parent: *How do you think the child’s blood glucose readings in the last month compare with how his/her readings are normally? Was the last month fairly typical?* The researcher will make note of any circumstances which were not typical such as illness, school holidays, etc.

The blood glucose readings downloaded at the home visits will be checked against the target ranges for in- and out-of-range readings. This will provide us with an indication of whether the intervention was helpful in bringing the blood glucose values into the target range at 1-month post-intervention and 6-month follow-up.

##### Diabetes team report

The target blood glucose ranges for each child will also be obtained from their diabetes team at the time of their enrolment in the study, which will be used to check for in- and out-of-range readings. Glycosylated haemoglobin (HbA1c) levels will be obtained from the child’s diabetes team at the time of their routine medical review. HbA1c levels provide an indication of an individual’s average blood glucose concentration over the previous 3 months, and are considered the best marker of longer-term diabetes control. As a reference point, the HbA1c levels are usually between 4.0 to 6.0 % in individuals who do not have diabetes. In Australia, HbA1c targets for children and adolescents with type 1 diabetes are <7.5 % [55, 56]. HbA1c levels of 8.0 % or above may indicate that tighter control of blood glucose levels is required. Similar to blood glucose values, change in HbA1c values will provide us with an indication of whether the intervention has an effect on longer-term glycaemic control.

#### Diabetes self-efficacy

##### Parent-report

The *Self-Efficacy for Diabetes Scale* (SED) [57] will be used to assess parents’ self-efficacy for managing their child’s diabetes. It contains 22 parenting tasks associated with diabetes management, and parents rate their confidence with performing each task on a 5-point scale (1*-Very sure I can’t* to 5*-Very sure I can*), indicating how much they believe they can or cannot do what is asked *now*. The scale has demonstrated good internal consistency (α = .87).

#### Family quality of life

##### Parent-report

Parent and family quality of life will be evaluated using the 36-item *PedsQL Family Impact Module* [59]. This measure encompasses six scales measuring parent self-reported functioning (physical, emotional, social and cognitive functioning, communication, worry), and two scales measuring parent-reported family functioning (daily activities and family relationships). This measure yields a total score (α = .97), and two summary scores [parent health-related quality of life (α = .96) and family functioning (α = .90)]. Parents rate each item from 0 (*Never*) to 4 (*Almost always*) depending on how true the statement was for them and their family in the past month. Similar to the *PedsQL Generic Core Scale,* items are reverse-scored and transformed on a scale from 0-100, with higher scores indicating better quality of life.

#### Parenting stress

##### Parent-report

General parenting stress will be evaluated using *The Parenting Stress Index/Short Form* (PSI/SF) [60], which is a 36-item self-report instrument designed to measure the relative magnitude of stress in a parent–child system and to identify the sources of stress. Parents respond to each statement using a 5-point scale (from *Strongly Agree* to *Strongly Disagree*), to indicate the degree to which that item describes their beliefs. The PSI yields three subscales, including Parental Distress, Parent Child Dysfunctional Interactions, and Difficult Child, as well as a Total Stress score. The PSI/SF is highly correlated with the full-length PSI instrument (*r* = .94), and the 2-week test–retest reliability of the full-length PSI with the PSI/SF is *r* = .95.

*The Parent Experience of Child Illness Scale* (PECIS) [61] is a 25-item self-report scale which assesses parents’ adjustment to the experience of their child’s chronic illness. Parents rate their thoughts and feelings over the past month on a 5-point scale from 0 (*Never)* to 4 (*Always*). This measure provides scores on four subscales: Emotional Resources (range 0–20), Long-Term Uncertainty (range 0–20), Guilt and Worry (range 0–44), and Unresolved Anger and Sorrow (range 0–32). This measure has acceptable reliability (ranging from α = .72–.89), and evidence of construct validity for all subscales.

#### Program satisfaction measures

##### Parent-report

Following the intervention, parents will complete a 13-item *Client Satisfaction Questionnaire* [62], which measures the participants’ satisfaction with the services they received. Parents use a 7-point scale to rate 10 items assessing the quality of the service received, the extent to which the program met their own and their child’s needs, and how much the program helped the parents develop skills and improve their child’s behaviour. The item scores will be summed to generate a total score ranging from 10 to 70, with higher scores indicating greater program satisfaction. The rest of the items are posed as open-ended questions. This measure is an adaptation of the Therapy Attitude Inventory [63], which has demonstrated high internal consistency (*α* = .88) and discriminant validity.

##### Child-report

Following the intervention, children will complete a 6-item *Child Satisfaction Questionnaire* [64], which addresses questions about the extent to which the child was aware of their parents undertaking a parenting program, and any changes that the child noticed in their parents’ interactions with them since participating in the program. Children will rate five items: whether they feel they are getting along better with their parents, how well their parents manage misbehaviour, whether they think that their parents learnt useful things in the program, whether their parents have been saying more nice things to them after the program, and if they are pleased that their parents did the program, on a 5-point scale, with responses ranging from *No* to *Heaps more*. The item scores will be summed to generate a total score, with higher scores indicating greater child satisfaction.

### Data management

All research investigators and the research coordinator will have full access to the data collected, and will be jointly responsible for data collection, data entry, analysis and write-up of results. To maintain the confidentiality of data, all hard copy records, such as screening interview forms, questionnaires, and consent forms, will be kept in a locked filing cabinet in a locked office at the University. Data from printed and online questionnaires, as well as blood glucose data, will be entered into a computer file. Digital recordings of home visit data will be stored in a computer file and backed up to external hard drives. Data in computer files will be kept in password-protected files within the University computer network. Security with regard to online questionnaires will be maintained by the University. Data collected from participants will be stored in a re-identifiable format for 7 years after completion of the project in accordance with ethics committee requirements. The chief investigators of the study will have access to the final trial dataset, and any request to access de-identified data will go through the chief investigators. Any publications arising from this research will be devoid of any identifying information and results will be reported in an aggregate form only. Full study protocol will be published in a peer-reviewed journal.

### Statistical analyses

Prior to conducting the main analyses, data will be screened for distributional assumptions (e.g., univariate and multivariate normality, outliers, and multi-collinearity) as well as inter- and intra-measure consistency. Preliminary analyses will also investigate whether the study groups differ on any demographic or clinical characteristics at baseline. Group differences in baseline characteristics will be examined via linear (for continuous outcomes) and logistic (for categorical outcomes) regression models. It is anticipated that the groups will not differ at baseline due to randomisation to study conditions. If baseline group differences are detected, we will investigate and report the extent to which the results from the planned analyses described below are altered, when these differences are statically controlled. For missing data points, an analysis of missing data will be conducted (see paragraph below on missing data) and imputation methods will be considered [65]. Data analysis will follow the intention-to-treat principle, which means that the study population subjected to the analysis will consist of all randomised individuals.

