### Design

The study is a 2 (Triple P vs CAU) × 3 (time: pre-test, post-test, 6-month follow-up) design superiority trial with 1:1 allocation ratio.

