### Participants

Participants will be 60 families of 2–10 year old children with type 1 diabetes, recruited through primary care settings, paediatric specialists, specialist clinics at major Brisbane hospitals, and through targeted mail-out and media campaigns. Diagnostic confirmation of the child’s diabetes will be sought from the child’s treating diabetes team.

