### Sample size and power analysis

The required sample size for the study was calculated to assure 80 % power to detect an effect size of ES = .5 for a mean difference in rates of change in the variables of interest between the groups (INT vs CAU and/or mother vs father vs child). This effect size is categorized as medium based on Cohen’s guidelines and has been chosen based on our previous research [35]. In multilevel models with repeated measures, the sample size is effectively the number of observations (the level-1), not number of participants (level-2 units). We performed power analysis using G*Power software [69] for rANOVA, looking at the within-between interactions and allowing for conservative estimate of intra-individual variability (.5). The analyses indicated that a sample size of 50 is sufficient to detect an ES of .5 at the significance level of .05 (two-tailed). This is without taking into account the added power accorded by the rich repeated measures in our data. Assuming 16 % attrition rate, an available sample of 60 families will be sufficient to detect medium sized effects.

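### Tests of baseline differences after randomisation decide whether, and for what, the supplementary adjusted analysis is run, and the planned model is not said to condition on the baseline outcome.

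*Protocol article*

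**What the plan says.** Under Statistical analyses, the protocol article plans preliminary comparisons of the arms on demographic and clinical characteristics: "Group differences in baseline characteristics will be examined via linear (for continuous outcomes) and logistic (for categorical outcomes) regression models". It expects no differences because families are randomised. It continues: "If baseline group differences are detected, we will investigate and report the extent to which the results from the planned analyses" change when the differences are controlled. No threshold for a detected difference is given, and the text does not say whether baseline outcome scores are among the characteristics tested.

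Under Primary analyses, the planned model is a multilevel model for repeated measurements, with group dummy codes as fixed effects and random intercepts and slopes. No baseline covariate is named. The Design section gives the occasions as "time: pre-test, post-test, 6-month follow-up", so the baseline score enters as the first of three responses. The sample size section frames the effect as a difference between groups in rates of change.

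**The concern.** Under randomisation any baseline difference is due to chance, so a test of it answers no useful question. Here the tests still have a job: they decide whether an adjusted analysis is reported and which variables it contains. A check chosen that way appears or not by luck, and its covariates are picked for their imbalance, not for their relation to the outcome. A moderate imbalance in a variable that does predict the outcome can pass with no check at all.

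The variable most clearly at issue is the baseline value of each outcome. If the planned effect is a contrast of change, baseline imbalance moves the estimate through regression to the mean, and the contrast is less precise than one that conditions on baseline. In a trial of 60 families with Bonferroni correction across outcomes, that loss of precision matters.

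**Working it through.** **Inputs from the protocol article**
- Size: "Participants will be 60 families" (Participants) and "superiority trial with 1:1 allocation ratio" (Design), so 30 per arm.
- Analysable number, effect and alpha: "a sample size of 50 is sufficient to detect an ES of .5 at the significance level of .05 (two-tailed" (Sample size and power analysis), so 25 per arm after dropout.
- Power target: "calculated to assure 80 % power to detect an effect size of ES = .5".
- Correlation: "allowing for conservative estimate of intra-individual variability (.5", read here as a correlation ρ = .5 between visits.

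**Assumptions**
- "Detected" means p < .05 per test.
- Tests are independent, with 10 to 20 characteristics tested. The article lists about 15 demographic and clinical items.
- Scores have SD 1 at each visit.

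**Plan's own figure.** 50 / (1 − .16) = 59.5, which rounds up to 60. The inflation for dropout reproduces. Nothing below depends on how the 50 was obtained.

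**Chance flags.** P(at least one) = 1 − .95^k.
- k = 10: .40
- k = 15: .54
- k = 20: .64

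**What the screen misses.** Smallest observed difference flagged = t(.975, 58) × √(2/30) = 2.002 × .258 = .52 SD. For one continuous variable, the chance of an observed imbalance above .3 SD is .25. Since .05 are flagged, .25 − .05 = .20 lie between .3 SD and the limit, unflagged.

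**Shift from imbalance in the baseline outcome.** Given a baseline difference D, a contrast of change has conditional expectation equal to the true effect − (1 − ρ)D. At ρ = .5:
- D = .3 gives a shift of .15 SD.
- D = .5 gives a shift of .25 SD.
- Averaged over chance imbalances of .3 to .5 SD (mean about .38), the shift is .5 × .38 = .19 SD, against a target of .5 SD.

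The shift runs opposite to the baseline difference. Over all randomisations it averages zero.

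**Precision at one follow-up**, in units of the single-visit variance: change contrast 2(1 − ρ); conditioning on baseline 1 − ρ².

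| ρ | Change | Conditioned | Variance saved |
|---|---|---|---|
| .3 | 1.40 | .91 | 35% |
| .5 | 1.00 | .75 | 25% |
| .8 | .40 | .36 | 10% |

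At ρ = .5 the ratio is 1.00 / .75 = 1.33, a third more variance for the change contrast. Standard errors with 30 per arm are √(1.00 × 2/30) = .258 and √(.75 × 2/30) = .224. Power for d = .5, two-sided .05, noncentral t:
- 30 per arm: 48% for change, 59% conditioned.
- 25 per arm: 41% for change, 52% conditioned.

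These powers refer to one follow-up with d in single-visit SD units. They show the relative loss and are not a recalculation of the plan's 80%.

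**Stable covariate.** Take a baseline characteristic correlated .5 with the outcome at every visit. Given an imbalance of .3 to .5 SD, simulation gives a shift of about .19 SD for the follow-up score alone but about 0 for the change contrast, because the characteristic cancels.

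**The case against.** The strongest defence is that the plan already ranks its results. The planned analyses are run whatever the tests show, and the adjusted version is reported only as a comparison with them. This stands. A reader might infer that the tests select the primary model, that the primary estimate is biased, or that nothing says which result counts. The text supports none of these: the planned analysis is implicitly primary, and the randomised estimate is unbiased over repeated randomisation. The .19 SD is a shift conditional on an unlucky baseline, which is a matter of precision.

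A reader might also infer that adjusting for child age or time since diagnosis would bring a similar gain. That is not shown. Such a variable cancels from a change contrast unless it predicts change, and the article gives no figures on that.

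Third, an article may leave covariate lists to a fuller document, and the stated fixed effects are too brief to rule out a model with equal baseline means, which would recover most of the lost precision. This stands in part. A missing list would be no finding; the point is the rule that the article does write, in which control for baseline follows detection. Baseline also already enters as a response, so the loss is relative to conditioning on it and shrinks as ρ rises.

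Finally, the flag rates rest on an assumed .05 and on independent tests, and a false flag costs only an extra reported analysis. Both are true, and they limit the point to the quality of the check.

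**Conclusion.** The point holds in a limited form. The test-then-adjust rule gives a supplementary check whose existence and content depend on chance: 40% to 64% for at least one flag over 10 to 20 tests, and no flag below about .52 SD with 30 per arm. It leaves the primary result as planned.

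The more material part concerns the baseline outcome. If the primary effect is the group difference in change, as the sample size section implies, and ρ is .5, an unflagged imbalance of .3 to .5 SD shifts the estimate by about .19 SD, and conditioning on baseline would save 25% of the variance. The saving would be 35% at ρ = .3 and 10% at ρ = .8. These sizes depend on reading the plan's .5 as a between-visit correlation and on a model that does not constrain baseline means.

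**What to change.** - Drop the baseline tests as a trigger for adjustment, and present baseline data by arm descriptively.
- State in advance that each primary model conditions on the baseline value of its outcome. Either enter baseline as a covariate with the two follow-up scores as responses, or keep all three occasions as responses and constrain baseline means to be equal across arms.
- If an analysis with further covariates is wanted, name one or two now and run it whatever the observed balance. Child age is a candidate for child-reported parenting, since the article's section on that measure says age affects how children respond.

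The cost is small: revised model wording and slightly more analysis work. The first option does change the response structure of the 2 × 3 model; the second keeps it. The baseline scores and child age are already collected.
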